| Observational Endpoints:                                                 | 
Cellular mediated immune (CMI) response
 
Secretion of a panel of Th1 (interferon-gamma [IFN-<math>\gamma</math>], tumor necrosis factor-alpha [TNF-<math>\alpha</math>], interleukin-2 [IL-2]), and Th2 (IL-5, IL-4, IL-10, IL-13) cytokines by peripheral blood mononuclear cells (PBMCs), upon in vitro re-stimulation with vaccine antigens will be quantified before the first vaccination and 8 days after the second vaccination.
                                                                                                                                                                                                                                                                                                                                              |
| Methodology/Trial Design:                                                | 
Phase II, multicenter, randomized, open trial. Subjects will be enrolled in a step-down design (based on age) following internal review of Day 0 to 7 safety data for each primary series vaccination from the previous age group.
 
Primary series vaccination at D0 and D21 and booster vaccination at either M6 or M12 (according to the Ab persistence data from GPA01 and GPA02).
                                                                                                                                                                                                                                                                                                                                                                                                       |

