***Trial description:***

After the Informed Consent Form (ICF) (to be signed by parent/legal representative for all subjects) and assent form (one for subjects aged 7 to 12 years [i.e.  $\geq 7$  to  $< 13$  years] and another for subjects aged 13 to 17 years [i.e.  $\geq 13$  to  $< 18$  years]) have been signed, eligible subjects will be randomized to receive primary vaccinations of 7.5  $\mu\text{g}$  HA without adjuvant or 30  $\mu\text{g}$  HA with adjuvant (Group 1 [9 to 17 years] and Group 2 [3 to 8 years]) or 3.75  $\mu\text{g}$  HA without adjuvant, 7.5  $\mu\text{g}$  HA without adjuvant, 15  $\mu\text{g}$  HA with adjuvant or 30  $\mu\text{g}$  HA with adjuvant (Group 3 [6 to 35 months]).

Both formulations (30 $\mu\text{g}$  HA + Ad and 7.5 $\mu\text{g}$  HA) are well tolerated with no safety signals raised following administration of a first and second dose in adults and the elderly subjects. Based on the available data, no safety concern is anticipated in children. However, as a precaution, subjects will only be enrolled after a satisfactory review of the Day 0 to 7 safety data for the previous vaccination and/or the previous age group. This process is represented in the following diagram:

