**Figure 3: Diagram to Show the Safety Data Review Process Prior to Inclusion of Subsequent Groups**

[figure not shown]

Sanofi pasteur safety committee will perform a formal review of safety within 7 days after the first vaccination of each cohort of subjects. The 2nd vaccination of the cohort and the first vaccination of the next cohort of age will depend on the recommendation given by sanofi pasteur after discussion with the Principal Investigators. Safety reports and conclusion from the sanofi pasteur safety committee will be forwarded to the IECs after each go/no go decision.

During the safety review meeting, sanofi pasteur safety committee will evaluate each SAE and examine the severity, duration of symptoms and the causal relationship according to the Investigator assessment. In addition, the safety committee will also focus on severe fever.

The safety profile will be compared to that observed in adult population.

This review might be escalated to the Product Safety Board for scientific and medical advice on any severe medical event in case significant findings are pointed out following safety review.

The safety committee will share the conclusions of safety review with the Principal Investigators. Within 24h following the meeting, the safety committee will send to the Principal Investigators and to the IECs the main conclusions of the meeting, and especially the decision for next cohort vaccination.

Then, the sanofi pasteur safety committee will provide a comprehensive report on safety data collected with its recommendations to Principal Investigators and IECs to pursue or not the vaccinations.

In case of trial modification/discontinuation, a meeting will be organized between the Principal Investigators and the Sponsor, to review recommendations and decide how the trial can be modified (modification of the subject follow-up, pause/stop the trial).

A booster vaccination will be performed at 6 or 12 monthsa after the first vaccination. Each subject will be followed up for 6 months after the booster vaccination, and will provide six, seven or eight blood samples (see Figure 1 and Figure 2).

Subjects will be observed for safety for 30 minutes after each vaccination, and any AE/reaction occurring during the 21 days after each vaccination will be recorded using a Diary Card (DC). In addition, all SAEs will be recorded during the entire trial (including the 6 month follow-up period).

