## 5.2 Discussion of Trial Design

In preparation for an influenza pandemic, the CHMP has developed licensing guidelines for pandemic influenza vaccines (14) (15). These guidelines describe an initial two-study approach for the development of a core dossier to facilitate the granting of a provisional license in the event that a pandemic occurs. The first study in this core dossier is a dose/formulation finding and the second is a larger study performed in adults and the elderly using dose(s) selected from the first study. These two studies are ongoing and will be included in the initial dossier as required by the CHMP guidelines.

Since children may be very vulnerable to infection, the CHMP guidelines also suggest that at least limited safety data should be obtained from healthy children to support the initial dossier of adult/elderly data. The present study has therefore been designed and will be conducted to address safety in this population and to gain the first information regarding the immune response of children to the dosages/formulations to be tested.

As such, this is a Phase II study, in which three age-groups (9 to 17 years, 3 to 8 years, and 6 to 35 months) will be studied. For safety reasons, groups will be studied in reverse order of age, with a thorough and satisfactory review of the Day 0 to 7 safety data for each primary series vaccination in Group 1 and Group 2 data being performed prior to the inclusion of subjects in Group 2 and Group 3, respectively. This safety review will be performed by the Sponsor's Clinical Team and will focus on clinically relevant events (severe fever in the 7 days following vaccination and SAEs). These data (excluding SAEs) will be provided unclean as a data listing by the Trial Data Manager and the SAEs will be provided by the Sponsor's Global Pharmacovigilance Department, and will be shared with the Investigators. The review will only be

escalated to a Product Safety Board if there are significant findings following the Clinical Team review.

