### **8.3.3.2 Reactogenicity (Solicited Reactions from D0 to D7 after each Vaccination)**

After vaccination, the subjects will be provided with a safety DC, a digital thermometer and a flexible centimeter ruler and will be instructed how to record the following items in the safety DC on the day of vaccination and daily for the next 7 days (i.e. D0 to D7).

- Maximum daily axillary temperature.
- Maximum daily measurement or maximum severity grade of all other solicited injection site or systemic reactions.
- Date of last day of presence of the reaction if it lasted beyond D7.
- Action taken for each event, if any (medication etc).

Tables 8.1, 8.2, 8.3 and 8.4 present the injection site and systemic reactions that will be pre-listed in the safety DCs and CRFs, together with the severity scales for subjects aged <2 years and subjects aged  $\geq 2$  years.

The D0 to D7 safety data following the two primary series vaccinations will be collected and reviewed at V02 and V04, 8 days after the vaccination. These data will be reviewed for Groups 1 and 2 by the Sponsor prior to progression to the next age group (Groups 2 and 3, respectively).

**Table 8.1: Solicited Injection Site Reactions: Definitions, Terminology and Severity Scales for Subjects Aged 6 months to <2 years**

|                         | Injection site tenderness                                                                                                                                                                                        | Injection site erythema                                        | Injection site swelling                                                                                                                                                                                                                                                                                                       | Injection site induration                                                                                                                                                                                                                                  |

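### The step-down gate is stated inconsistently: Section 5.1.2 ties the next age group's first dose to a review after the first vaccination, while three other places require D0-D7 data after both primary vaccinations

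*Protocol*

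**What the plan says.** All of the following is current protocol text.

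- **Section 5.1.2, text under Figure 3.** "Sanofi pasteur safety committee will perform a formal review of safety within 7 days after the first vaccination of each cohort of subjects". The next sentence sets out what hangs on that review: "The 2nd vaccination of the cohort and the first vaccination of the next cohort of age will depend on the recommendation" given by the sponsor after discussion with the Principal Investigators. The text describes no separate review after the second dose.
- **Section 5.1.2, sentence introducing Figure 3.** Enrolment follows a satisfactory "review of the Day 0 to 7 safety data for the previous vaccination and/or the previous age group".
- **Synopsis, Methodology/Trial Design.** Subjects are enrolled "following internal review of Day 0 to 7 safety data for each primary series vaccination from the previous age group".
- **Section 5.2.** The age groups are studied in descending order, with a "review of the Day 0 to 7 safety data for each primary series vaccination in Group 1 and Group 2 data being performed prior" to inclusion in Groups 2 and 3 respectively. The reviewer is the Sponsor's Clinical Team.
- **Section 8.3.3.2.** "The D0 to D7 safety data following the two primary series vaccinations will be collected and reviewed at V02 and V04", followed by "These data will be reviewed for Groups 1 and 2 by the Sponsor prior to progression to the next age group".

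Sections 1.3 and 5.1.1 mention D0-D7 data from the preceding group without saying after which dose.

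**The concern.** The step-down by age is the protocol's stated precaution for younger children, so the text should give one answer to a simple question: which of the older group's vaccinations must have been reviewed before the next group receives its first dose? Section 5.1.2 points to the first. The Synopsis and Sections 5.2 and 8.3.3.2 point to both.

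Two smaller inconsistencies sit in the same passages. The reviewer is the safety committee in Section 5.1.2, the Clinical Team in Section 5.2 and simply the Sponsor in Section 8.3.3.2. And Section 5.1.2, read literally, places the review no later than seven days after vaccination, while the D0-D7 diary data are reviewed at V02, on D8 (+1).

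What is at stake is whether a given decision to open Group 2 or Group 3 conforms to the protocol, and whether the ethics committees that receive it can tell.

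**Working it through.** **Step 1: compare the rules.**

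| Place | Data required before the next age group | Reviewer |
|---|---|---|
| Section 5.1.2, under Figure 3 | Review after the first vaccination | Safety committee |
| Section 5.1.2, introducing Figure 3 | Previous vaccination, previous age group, or both | Not named |
| Synopsis | D0-D7 after each primary vaccination | Internal |
| Section 5.2 | D0-D7 after each primary vaccination | Clinical Team |
| Section 8.3.3.2 | D0-D7 after both, from V02 and V04 | Sponsor |

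**Step 2: test a rolling reading.** A review of each vaccination could mean that dose-1 data release the next group's dose 1 and dose-2 data release its dose 2. That would remove the conflict. But Section 5.2 places the review before subjects are included in the next group, and Section 8.3.3.2 places it before progression and names V04, which falls after the second dose. The rolling reading therefore fails for those two sections.

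**Step 3: time between the two gates.** Inputs from Figures 1 and 2 and Section 5.1.3: V02 is 8 days (+1) after dose 1; dose 2 is at D21 ± 3; V04 is 8 days (+1) after dose 2. Days are counted from D0 of the last subject in a cohort.

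- Dose-1 data complete: D8 to D9.
- Two-dose data complete: nominal 21 + 8 = D29; earliest 18 + 8 = D26; latest 24 + 9 = D33.
- Difference per step: nominal 29 − 8 = 21 days; smallest 26 − 9 = 17; largest 33 − 8 = 25.
- Over two steps: 2 × 8 = 16 to 2 × 9 = 18 days, against nominal 2 × 29 = 58 (2 × 26 = 52 to 2 × 33 = 66).

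**Step 4: evidence at each gate.** Groups 1 and 2 have 60 children each. The first-dose gate rests on 60 administrations in 60 children. The two-dose gate rests on up to 120 administrations in the same 60 children.

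**Step 5: does the calendar show which rule was meant?** Table 5.1 gives June to September 2007 for both inclusion and primary vaccination, at most 121 days (1 June to 30 September). From the first group's D0 to the last group's dose 2, with no time added for enrolment or for the review itself, the nominal minimum is 16 + 21 = 37 days under the first-dose gate and 58 + 21 = 79 days under the two-dose gate. Both fit within 121 days. The table is given by month and is described as indicative, so it does not decide the matter.

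**Step 6: the plan's own design figure.** Section 11.3 gives the chance of seeing at least one adverse event of 1% incidence: 1 − 0.99^240 = 91.0% and 1 − 0.99^120 = 70.1%. Both match the stated figures, and neither depends on the gate.

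**The case against.** The best defence is that the rules are cumulative. Section 5.1.2 says the next cohort's first dose depends on the recommendation; it does not say that the first-dose review is sufficient. It also speaks of each go/no-go decision, which allows for more than one. A sponsor that reviewed dose 1 and then also waited for dose-2 data would satisfy every section. That is true, but no passage states it, and Section 5.1.2 alone reads naturally as a single review releasing both next steps. Figure 3 was not visible in the text available for this review and may show the intended sequence. It could favour one reading, but it cannot change the wording of the other sections.

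Several stronger inferences are tempting, and the documents do not support them:

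- *The two sites might open cohorts on different evidence.* Section 5.1.2 makes the go/no-go a central sponsor decision, sent to the Principal Investigators and ethics committees within 24 hours of the meeting. Sites do not decide for themselves.
- *No second-dose data from the older group would exist when younger children are first vaccinated.* Under the first-dose reading none are required. Whether some exist depends on enrolment pace and review timing. Section 1.3 also says that adult D0-D42 data from GPA02 will be available at the start of the trial.
- *The change of reviewer is a move between independent and internal review.* Every body named is internal to the sponsor, and Sections 5.1.2 and 5.2 describe a similar focus (serious events and severe fever) and escalation to the same Product Safety Board. This is a question of naming and responsibility. The uncleaned listings in Section 5.2 make no contrast either, because Section 5.1.2 says nothing about data cleaning.
- *Section 5.1.2 prevails because it is newer.* The rationale for Amendment 1 in Section 1.3 says the working of this review was clarified. That suggests the other sections were not updated, but does not prove it.

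**Conclusion.** The inconsistency is real and should be fixed before the gate is used. One section ties step-down to a review after the first vaccination, three places require data after both, and the and/or sentence in Section 5.1.2 does not settle it. A decision could therefore comply with one section and breach the others. Opening Group 2 (60 children) and Group 3 (120 children aged 6 to 35 months) could each take place about 21 days (17 to 25) before the older group's two-dose D0-D7 data are complete.

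The day counts assume that the last subject in a cohort sets the date and that the review itself takes no time. No endpoint, analysis or sample-size figure is affected. That three places agree against one does not show which rule was intended, and no view is taken here on which is right. The reviewer's name and the seven-day timing are secondary points to be cleared up in the same edit.

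**What to change.** Reconcile the Synopsis methodology entry, both passages of Section 5.1.2 together with Figure 3, Section 5.2 and Section 8.3.3.2, so that all of them state the same three things:

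1. which vaccination or vaccinations of the older group must have been reviewed before the next age group is included;
2. a review time consistent with when the D0-D7 data are collected (V02 and, if applicable, V04);
3. one named body that takes the decision or, if the safety committee and the Clinical Team have different roles, what each does.

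The choice of rule belongs to the sponsor and the ethics committees. The cost is wording in an amendment. If the confirmed gate requires two-dose data and the calendar had assumed first-dose data only, it adds about three weeks per step, or nominally 58 − 16 = 42 days over both.

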**Table 5.1: Planned Trial Calendar for 6 and 12 Month Booster Designs**

|                                                    | 6 month booster design | 12 month booster design |
|----------------------------------------------------|-------------------------------|--------------------------------|
| Planned trial period (FVFS* to LVLS*)       | June 07 to September 08       | June 07 to March 09            |
| Planned Inclusion period (FVFS* to FVLS*)   | June 07 to September 07       | June 07 to September 07        |
| Planned primary vaccination period          | June 07 to September 07       | June 07 to September 07        |
| Planned booster vaccination period          | December 07 to March 08       | June 08 to September 08        |
| Planned end of trial†                       | September 08                  | April 09                       |
| Planned date of final clinical trial report | November 08                   | May 09                         |
| Expected trial duration for each subject    | 12 months                     | 18 months                      |

\* First visit of first subject; LVLS: Last visit of last subject; FVLS: First visit of last subject (last first visit).

† End of trial is defined as the date of the last contact with a trial subject within the scope of the trial.

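### The rule that opens the next age group is stated two ways: section 5.1.2 ties it to a first-dose review, while the synopsis, 5.2 and 8.3.3.2 require reviewed data after both primary doses

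*Protocol*

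**What the plan says.** The trial enrols three age groups in descending order: 60 children aged 9 to 17 years, 60 aged 3 to 8 years and 120 aged 6 to 35 months. The gate between them is described in several places in the protocol.

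- **Section 5.1.2, text under Figure 3.** "Sanofi pasteur safety committee will perform a formal review of safety within 7 days after the first vaccination of each cohort of subjects". Two steps are then attached to it: "The 2nd vaccination of the cohort and the first vaccination of the next cohort of age will depend on the recommendation given by sanofi pasteur". The investigators are to be consulted first. No review after dose 2 is defined there.
- **Synopsis, Methodology/Trial Design.** Enrolment steps down "following internal review of Day 0 to 7 safety data for each primary series vaccination from the previous age group".
- **Section 5.2.** A satisfactory Day 0 to 7 review is required, "for each primary series vaccination in Group 1 and Group 2 data being performed prior to the inclusion of subjects in Group 2". The same condition holds between Group 2 data and entry to Group 3.
- **Section 8.3.3.2.** Data after the two primary vaccinations are collected at V02 and V04, and "These data will be reviewed for Groups 1 and 2 by the Sponsor prior to progression to the next age group".
- **Section 5.1.2, trial description.** Subjects enter only after "a satisfactory review of the Day 0 to 7 safety data for the previous vaccination and/or the previous age group".
- **Section 5.1.1.** A satisfactory Day 0 to 7 review of the previous group is required, with no dose named.

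The reviewer also has two names. It is the sponsor's safety committee in 5.1.2, while 5.2 says "This safety review will be performed by the Sponsor's Clinical Team".

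**The concern.** The step-down gate is the main design protection for the 180 younger children (60 in Group 2 and 120 in Group 3). It fixes how much paediatric safety experience must be reviewed before the next age group is first injected.

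The protocol gives two different amounts. One is first-dose data only. The other is data after both doses of the primary series. An ethics committee that approved the trial on the synopsis or 5.2 would expect second-dose reactogenicity in the older group to be known first. A sponsor team working from 5.1.2 could open the next group without it and still be following the text.

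**Working it through.** **Inputs**

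- V02 is 8 days (+1) after dose 1; dose 2 (V03) is on D21 ± 3; V04 is 8 days (+1) after dose 2 (Figures 1 and 2; section 5.1.3).
- Groups 1 and 2 have 60 children each, 30 per formulation (synopsis, planned sample size).
- The 7 days in the 5.1.2 sentence are read as the data window, because the Day 0 to 7 diary data are first checked at V02 on D8.

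**The statements side by side**

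| Place | Data required before the next age group |
|---|---|
| 5.1.2, under Figure 3 | The only review defined follows dose 1 |
| Synopsis; 5.2 | Each primary vaccination of the previous group |
| 8.3.3.2 | Both primary vaccinations (V02 and V04) |
| 5.1.2, trial description | Either, because of the and/or |
| 5.1.1 | Not specified by dose |

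**Earliest opening of the next group**, in days from dose 1 of the last child in the older group, before any review time:

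- First-dose rule: last V02 = day 8 to 9.
- Two-dose rule: last V04 = 21 + 8 = day 29 nominally; 18 + 8 = 26 at the earliest and 24 + 9 = 33 at the latest.
- Difference, with the same delay at V02 and V04: (dose-2 day + 8) − 8 = dose-2 day = 21, range 18 to 24.
- Two steps, to the opening of Group 3: 2 × 21 = 42 days nominally.

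**Reviewed second-dose data at opening**

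- First-dose rule: none from the immediately preceding group. If one recommendation releases both steps, that group has not yet had dose 2.
- Two-dose rule: up to 60 children from that group, 30 per formulation.

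**Whether the calendar settles it.** Table 5.1 puts the row "Planned primary vaccination period" at June to September 2007, which is 121 days if it runs from 1 June to 30 September (an assumption, since only months are given). Before enrolment and review time, dose 2 in Group 3 falls nominally on day 8 + 8 + 21 = 37 under the first-dose rule and on day 29 + 29 + 21 = 79 under the two-dose rule. The longer schedule leaves 121 − 79 = 42 days for enrolment and review. The documents give no enrolment rate, and section 5.1.4 calls the calendar indicative, so it does not show which rule was meant.

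**The plan's own figures.** Section 11.3 reproduces: 1 − 0.99^240 = 0.910 (stated as above 90%) and 1 − 0.99^120 = 0.701 (stated as 70%). Neither depends on the gate.

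**The case against.** The best reply is that 5.1.2 states a necessary condition, not a sufficient one. Both steps depend on a recommendation, but the text does not say that one recommendation releases both. The same section speaks of reporting after each go/no go decision, so more than one is foreseen. Figure 3, which depicts the process, is not shown. One scheme would satisfy every statement: a first-dose review gates dose 2, and two-dose data gate the next age group. Sites would also not act alone, because the sponsor sends its conclusions and the decision on the next cohort to the Principal Investigators and ethics committees within 24 hours.

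Part of this stands. The combined scheme is possible and may well be what was meant, and central communication makes it unlikely that sites would apply different rules. But the scheme is nowhere stated. The only review that 5.1.2 defines follows dose 1, and the next age group is tied to it in the following sentence. The rationale for Amendment 1 lists the functioning of this review among the points clarified, yet the amended text still carries both rules.

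Three stronger inferences should be resisted.

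- **That infants would start with no second-dose experience in any child.** Count from dose 1 of the last Group 1 child. Under the first-dose rule, Group 3 opens on day 16 to 18 + S + 2r, where S is the Group 2 enrolment span and r the review lag, both in days. Group 1 finishes dose 2 on nominal day 21. So all of Group 1 has had dose 2 once S + 2r reaches 3 to 5 days (6 to 8 if dose 2 falls on D24), which is likely. What is missing is any requirement in 5.1.2 to review those data.
- **That the sections conflict on the infants' own dose 2.** They do not. Sections 5.2 and 8.3.3.2 concern progression to a next group, and Group 3 has none. Section 5.1.2 covers every cohort, and nothing contradicts it.
- **That two separate bodies are meant.** Both names denote sponsor-internal review of SAEs and severe fever with escalation to the Product Safety Board. This is largely a naming difference.

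**Conclusion.** The conflict is real and should be fixed. The 5.1.2 wording under Figure 3 lets the next age group open on a first-dose review; the synopsis, 5.2 and 8.3.3.2 require reviewed data after both primary doses. At each of the two steps the difference is whether any second-dose data from the immediately preceding group have been reviewed, and about 21 days (18 to 24) in opening date.

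This rests on reading 5.1.2 as one recommendation governing both steps, and on the visit windows as scheduled. It needs no enrolment rate. Figure 3 could show the intended order but could not make the sentences agree. No estimate, sample size or detection probability changes. The consequence is confined to the safety information required before younger children are exposed.

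**What to change.** Amend the text under Figure 3 in section 5.1.2 to describe two reviews:

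1. After dose 1 in every cohort, including Group 3, the Day 0 to 7 data collected at V02 are reviewed, and a favourable decision releases that cohort's own dose 2.
2. After dose 2 in Groups 1 and 2, the Day 0 to 7 data collected at V04 are reviewed, and a favourable decision releases the next age group.

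Remove the and/or from the trial description in 5.1.2, check Figure 3 against the new wording, and use one name for the reviewing body in 5.1.2 and 5.2. The synopsis, 5.2 and 8.3.3.2 already state the age-group rule and need no change to it.

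The cost is wording only, with no added visits, samples or subjects. Compared with the 5.1.2 reading, each younger group opens about three weeks later, a delay that the other three places already imply.
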